## Abstract

**Background:**

The increasing incidence of fatal opioid overdose is a public health crisis in Canada. Given growing consensus that this crisis is related to the presence of highly potent opioid adulterants (e.g., fentanyl) in the unregulated drug supply, drug checking services (DCS) have emerged as part of a comprehensive approach to overdose prevention. In Canada’s largest city, Toronto, a network of DCS launched in 2019 to prevent overdose and overdose-related risk behaviors. This network employs mass spectrometry technologies, with intake sites co-located with supervised consumption services (SCS) at three frontline harm reduction agencies. The protocol and rationale for assessing the impact of this multi-site DCS network in Toronto is described herein. The aims of this study are to (1) evaluate the impact of DCS access on changes in and factors influencing overdose and related risk behaviors, (2) investigate the perceived capacity of DCS to prevent overdose, and (3) identify composition (qualitative and quantitative) trends in Toronto’s unregulated drug supply.

**Methods:**

We will use a parallel-mixed-methods design with complementary data sources (including data from chemical analysis of drug samples, quantitative intake and post-test surveys, SCS, coroners, paramedic services, and qualitative interviews), followed by a meta-inference process wherein results from analyses are synthesized.

**Results:**

Whereas most DCS globally target “recreational drug users,” in Toronto, this networked DCS will primarily target marginalized people who use drugs accessing frontline services, many of whom use drugs regularly and by injection. This evolution in the application of DCS poses important questions that have not yet been explored, including optimal service delivery models and technologies, as well as unique barriers for this population. Increasing information on the unregulated drug supply may modify the risk environment for this population of people who use drugs.

**Conclusions:**

This study addresses evidence gaps on the emerging continuum of overdose prevention responses and will generate critical evidence on a novel approach to reducing the ongoing high incidence of drug-related morbidity and mortality in Canada and elsewhere.

## Background

The increasing incidence of fatal opioid overdose is a public health crisis in Canada. From January to September 2018, there were 3286 opioid-related deaths in Canada, corresponding to a death rate of 11.8 per 100,000 population (compared to 11.1 and 8.4 per 100,000 population in 2017 and 2016, respectively) [1]. In the western province of British Columbia, opioid overdose deaths have contributed to a decline in life expectancy, particularly among the most socioeconomically disadvantaged and marginalized communities [2]. In the province of Ontario, opioid overdose is now the leading cause of accidental death for young people, with one of every eight deaths among individuals aged 25 to 34 years involving an opioid [3]. With 308 opioid-related deaths in 2017, the country’s largest city, Toronto, Ontario, has experienced a 125% increase in deaths compared to 2015 [4]. There is now a consensus that the rising incidence of overdose is related in large part to the emergence of highly potent opioids, such as fentanyl and fentanyl analogs, in the unregulated drug supply. For example, fentanyl is present in an increasing number of overdose fatalities in Canada, though overdose deaths excluding fentanyl have remained relatively stable [5]. In Ontario, the presence of fentanyl in opioid-related deaths increased by 548% between 2006 and 2015 [6]. In 2017, there were 1265 opioid-related deaths in the province and fentanyl was present in 63.6% of these deaths; in contrast, fentanyl was present at death in 40.7% of 867 opioid-related deaths in 2016 [7]. This trend has thus accelerated in recent years, and fentanyl has overtaken heroin as the opioid most commonly present in opioid overdose deaths in Toronto [4]. In response, Canada’s federal government has characterized the current situation as a national public health crisis and allocated CAD$116 million in 2017 to a public health emergency response coordinated by Health Canada [8, 9], while the Government of Ontario committed CAD$280 million over 3 years to address the opioid overdose crisis [10].

Against this backdrop [11], drug checking services (DCS) have emerged as part of a comprehensive approach to preventing overdose mortality [12, 13]. Stakeholders—including the Federal Standing Committee on Health [14], Toronto Board of Health [15], and Mayors’ Task Force on the Opioid Crisis [16]—have identified DCS as a critical tool within a comprehensive plan to prevent overdoses related to the use of high-potency unregulated opioids. As a harm reduction intervention available in Europe since the 1990s, DCS provide information on the composition of drugs to their clients in order to facilitate more informed drug-related decision-making and to increase the capacity of individuals to avoid ingesting unanticipated toxic substances, which can lead to overdose and death [17, 18]. By aggregating analytic data on drug samples, DCS can also provide insight into trends in the unregulated drug supply [19–26]. The Canadian federal government has identified DCS as a key component of their response to the opioid overdose crisis and has committed to authorizing and funding pilot projects providing DCS at supervised consumption services (SCS) [27]. This includes funding over 5 years for the implementation of a multi-site DCS network in Toronto with the primary aim of reducing overdose deaths among structurally vulnerable individuals reliant on the unregulated opioid supply [28]. Launched in 2019, the DCS network in Toronto is located within frontline harm reduction agencies offering SCS and employs liquid chromatography and gas chromatography-mass spectrometry (LC- and GC-MS), the gold standards in forensic drug analysis [29], making Toronto’s DCS unique among Canadian DCS [30].

To date, evaluations of DCS have been limited to “recreational drug users” in nightlife settings in Europe [19, 31, 32], and no DCS employing LC- or GC-MS analysis for point of care services and operating within SCS have been scientifically evaluated. Herein, we describe the methodology for a study assessing the impact of a multi-site DCS network in Toronto. The overall goal of the this study is to determine whether access to DCS, to be co-located with SCS at three frontline harm reduction agencies in Toronto, is associated with a reduction in the incidence of overdose and related risk behaviors resulting from the consumption of unknown or toxic unregulated drugs by people who use drugs accessing frontline services, including young people who use drugs. The study has three specific aims: (1) evaluate the impact of DCS access on changes in and factors influencing overdose and related risk behaviors, (2) investigate the perceived capacity of DCS to prevent overdose, and (3) identify composition (qualitative and quantitative) trends in Toronto’s unregulated drug supply. Given the limited evidence on the influence and impact of DCS for subpopulations of people who use drugs regularly or by injection, this research study will represent a novel contribution to the scientific literature and provide important insights on DCS as an overdose prevention intervention. The protocol and rationale for this study is itself an important contribution to the literature, as it provides full study transparency and will be useful to researchers planning to evaluate DCS in other jurisdictions.

## Methods

### Conceptual framework

We employed Rhodes’ risk environment framework, which posits that physical, social, economic, and policy environments influence an individual’s health decision-making [33]. Drug policy changes in Canada—such as expanded access to naloxone (a medication that blocks the effects of opioid overdose), the adoption of legislation providing amnesty from drug possession charges for those calling emergency services in an overdose situation, and the scale-up of SCS—have modified the risk environment for people who use drugs to allow this population to avoid a range of drug-related risks. However, these responses are generally limited to addressing the needs of individuals during or after drug use, rather than before. In contrast, DCS are intended to provide people who use drugs with critical information so they can make informed decisions and take action prior to their use of unregulated drugs, thereby possibly preventing overdose from occurring in the first place. This is important given that an examination of the current risk environment experienced by people who use drugs in Toronto suggests that, while the emergence of fentanyl and fentanyl analogs in the unregulated drug supply is a macro-level factor in the increased incidence of fatal overdose and drug-related harm, social (e.g., experiences of trauma, ongoing stigma), economic (e.g., poverty), and policy (e.g., criminalization of drugs, lack of information on drug supply, low levels of access to social services) barriers constrain the capacity of individuals to avoid overdose risk [34, 35]. Applying Rhodes’ risk environment framework to this research study, DCS are defined as meso-level interventions that have the capacity to expand the range of choices that individuals reliant on the unregulated drug supply have to avoid overdose. This conceptual framework will guide variable selection for quantitative analyses and domains of interest for qualitative interviews. For instance, the study will examine the neighborhood in which drugs were purchased given that this factor shapes the meso- and micro-level economic risk environments [36] experienced by participants that may influence overdose risk. Gender and age will also be considered in the study to situate experiences of access to DCS and resulting outcomes given that the risk environment for drug-related harms is different across genders and ages [37, 38]. Qualitative interviews will investigate the influence of DCS on individuals’ perceived barriers to adopting overdose risk reducing behaviors.

### Approach

By employing complementary data sources—including data from analysis of drug samples, quantitative intake and post-test surveys, SCS, coroners, paramedic services, and qualitative interviews—this study will comprehensively evaluate the impact of DCS on a range of policy-relevant drug-related outcomes, while considering the impacts of co-located SCS (refer to Table 1: Measures, Outcomes, and Data Sources). A mixed-methods approach followed by a meta-inference process will be used to maximize multiple data sources and synthesize results of quantitative and qualitative analyses.

**Table 1 Tab1:** Measures, outcomes, and data sources

Measures and outcomes	Data sources
Aim 1: Evaluate the impact of DCS access on changes in and factors influencing overdose and related risk behaviors	
Self-reported overdose among those that access DCS and those that do not	– Quantitative survey data (intake) – SCS client data
Proportion of participants reporting increase in protective behaviors (not using alone, carrying naloxone, use of SCS, consultation with staff, smaller/) “tester” dosage, discarding toxic substances)	– Quantitative survey data (intake/post-test) – SCS client data
Proportion of participants reporting they gained, intend to use, and/or used knowledge and skills	– Quantitative survey data (post-test) – Qualitative interviews
Aim 2: Investigate the perceived capacity of DCS to prevent overdose	
Characterize participant perceptions on the capacity of DCS to alter the risk of overdose	– Qualitative interviews
Identify participant perceptions of contexts, facilitators, and barriers to the use of DCS	– Qualitative interviews
Aim 3: Identify trends in the composition (qualitative and quantitative) of the unregulated drug supply in Toronto	
Number of analysis results detecting composition different from participant expectations	– Quantitative survey data (intake) – Drug sample analysis data
Increase in accuracy and timeliness of alerts in response to dangerous drug trends	– Drug sample analysis data – Qualitative interviews
Spatial association between frontline harm reduction agencies with DCS and fatal overdose, and changes over time	– First responder and coroner data (from OCC and TPaS)

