### Data collection

#### Intake and post-test surveys (Aim 1)

Intake and post-test surveys will be administered to all consenting DCS clients at the three sites in Toronto, including participants who access DCS once and those who access DCS multiple times, allowing for a combined use of cross-sectional and longitudinal approaches. Surveys will be administered by frontline staff on an electronic tablet with the option for self-administration depending on the needs of the participant. Guided by the abovementioned conceptual framework, demographic and drug-using factors will be collected at first visit to DCS via a baseline intake survey to assess the influence of additional vulnerabilities facing key populations. An anonymous identifier will be created in the baseline intake survey and linked to intake surveys completed at subsequent visits. Questions on the intake survey, administered at every visit to DCS, include the following: What substance participants believe they are having tested?; When and where they purchased the substance?; and, If they are sharing the results with others, with how many people? Post-test surveys conducted immediately after analysis results are provided will query participants about their intended behaviors in response to analysis results, as well as allow frontline staff to record other services accessed (e.g., SCS, naloxone) and observed behaviors (e.g., discarding remainder of drug that was tested).

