#### SCS client survey data (Aim 1 substudy)

An ongoing longitudinal cohort is collecting data from people who inject drugs who do and do not use SCS at the three frontline agencies participating in the DCS network. This allows for harmonization of survey tools across both projects. As such, for participants consenting to linkages, data from a standardized SCS cohort survey (e.g., age, gender, neighborhood of residence, and drug-using factors) and data from the SCS pre/post injection assessment form (e.g., overdose outcomes, whether emergency medical attention was provided [i.e., SCS staff response and/or call to 911 for paramedic response], naloxone administered) will be accessible for consenting participants. This will also allow for a substudy consisting of a comparison of outcomes (i.e., overdose incidence and related risk behaviors) among frontline agency clients who access SCS exclusively, who access both SCS and DCS, and who access neither.

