### Analytic plan

#### Multivariable model of participant overdose risk behaviors (Aim 1)

For participant survey binary outcomes, we will employ either population-averaged models (i.e., generalized estimating equations; GEE) or subject-specific models (generalized linear mixed models; GLMM) with binomial distribution and logit link. The primary outcome is recent (i.e., past 6 months) self-reported overdose; the primary exposure is a categorical measure of frequency of DCS access over the past 6 months. GEE will be used if participant visits are equally distributed over time and if we have low levels of missing data. In the case of unequal distribution of participant visits over time and/or substantial missing data, we will employ GLMM. These models efficiently address problems of missing data and variable timing of subject visits. Both GEE and GLMM are suited to the analysis of longitudinal data, as they can account for both within-subject correlation and between-subject differences with results also remaining highly interpretable. We will initially model temporal correlations between subject responses using an autoregressive structure, with subject-specific variances and correlations assumed to decline exponentially over time; this is critical given that we anticipate variance in client follow-up times. GLMM models will also include independent time-varying variables from the linked intake and post-test surveys as potential confounders. This will allow for a “pre versus post” test evaluation using longitudinal DCS data. To assess potential bias as a result of loss to follow-up, sociodemographic and drug-related factors collected on the intake and post-test surveys will be compared among participants who only completed a baseline DCS visit and those that accessed the service repeatedly. Multilevel multiple imputations may also be considered if needed.

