
## Discussion

A crucial difference between the adoption of DCS in Toronto and the longstanding use of this harm reduction service throughout Europe is the targeted subpopulation of people who use drugs. Whereas most DCS globally target “recreational drug users,” in Toronto, DCS will primarily target marginalized people who use drugs accessing frontline services, many of whom use drugs regularly and by injection. This evolution in the application of DCS poses important questions that have not yet been explored, including optimal service delivery models and technologies, as well as unique barriers for this population. As the only DCS in Canada employing LC- and GC-MS analysis for point of care services, it will be important to compare results with DCS currently operating in British Columbia and Ottawa employing different and less sophisticated technologies (e.g., Fourier-transform infrared spectroscopy, fentanyl test strips), including in terms of the capability of technologies to detect drug market trends and respond to local drug use patterns. Although employing LC- and GC-MS for the analysis of drug samples has the potential to offer clients more information than the use of other technologies, the time required to receive analysis results may not be suitable for all populations of people who use drugs. It remains to be seen whether participants will consume their substance before receiving analysis results, and if they will modify their behaviors in response to analysis results, particularly when a high-potency opioid is detected.

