### Limitations

The study has limitations typical of community-based intervention evaluations. Since denying access to DCS is not ethical or feasible, the recruitment process is being integrated directly into the delivery of DCS. While this will allow for the collection of data from a large proportion of the population of DCS clients, it does present limitations. For instance, it is not possible to estimate the number of individuals that will access DCS and provide data, nor the total person-time of data. Second, we note challenges in disentangling the impact of SCS and DCS on overdose incidence and related behaviors given that these two interventions will be co-located in our study setting. However, the 1-year delay between the implementation of SCS and that of DCS provides an ideal natural experiment to test the independent effects of these interventions. Further, the harmonization of data collection tools between SCS and DCS evaluations will further allow for the assessment of independent effects as we are able to evaluate outcomes among SCS clients who do and do not use DCS. Another limitation is the absence of a comparison group, except for the SCS sub-analysis. A final challenge worth noting is that while we would prefer that participants create an anonymous identifier, since this would allow us to link their data from separate visits to DCS and therefore employ panel approaches, this will depend upon the willingness of clients to consent to participating in the research, creating an anonymous identifier, and consistently recording their survey responses under their identifier at subsequent visits.

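### The Table 1 behavior measure counts only increases, so on its own it cannot show reduced caution and would exceed zero with no true change

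*Protocol article*

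**What the plan says.** Table 1, in the Approach section of the Methods, lists under Aim 1 the "Proportion of participants reporting increase in protective behaviors". Six behaviors follow in parentheses. Four are "not using alone, carrying naloxone, use of SCS, consultation with staff"; the others are taking a smaller or tester dose and discarding toxic substances. The sources given for this row are the intake and post-test surveys and SCS client data. The row names neither decreases nor net change.

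The aim it serves, as worded in the Background, is to "evaluate the impact of DCS access on changes in and factors influencing overdose and related risk behaviors". That wording has no direction.

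Four other places bear on the point:

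- **Intake and post-test surveys (Aim 1):** post-test surveys "will query participants about their intended behaviors in response to analysis results", and staff record services used and observed acts such as discarding.
- **Limitations:** "Another limitation is the absence of a comparison group, except for the SCS sub-analysis".
- **Discussion:** it is left open whether participants will consume the drug before the result is known, and "if they will modify their behaviors in response to analysis results, particularly when a high-potency opioid is detected".
- **Multivariable model (Aim 1):** the primary outcome is self-reported overdose in the past 6 months, so the behavior measure is not primary.

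**The concern.** A proportion of increasers is a one-sided count. Its expected value under no effect is not zero whenever reports vary within a person, and participants who become less cautious are counted together with those who do not change. Anyone already performing a behavior at first intake cannot increase but stays in the denominator.

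For a drug checking service, less caution after a reassuring result is an obvious adverse path, and Aim 1 is worded broadly enough to include it. A reader who sees only this row could take ordinary fluctuation, or a tendency to report what staff hope to hear, as benefit. The main sample has no comparator from which to judge how large the figure would be without the service.

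**Working it through.** The article states no figure for this measure, so there is nothing to reproduce. It also gives no prevalence or within-person correlation for any behavior; the values below are assumptions.

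**1. No true change, with increase read as a difference between two reports.** Let a yes/no behavior have prevalence p at both times and within-person correlation ρ. Then

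P(increase) = P(decrease) = p(1 − p)(1 − ρ).

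- Lowest value in the assumed range (p = 0.3 or 0.7, ρ = 0.9): 0.21 × 0.1 = 0.021, or 2.1%.
- Middle value (p = 0.5, ρ = 0.5): 0.25 × 0.5 = 0.125, or 12.5%.
- Highest value (p = 0.5, ρ = 0.3): 0.25 × 0.7 = 0.175, or 17.5%.

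The same share decreases in each case, so the net change is 0. If all 1080 expected clients gave two linked reports, 2.1% to 17.5% would be about 23 to 189 people. The article cannot say how many will return, so these counts only convey scale.

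**2. A true fall.** Let prevalence drop from p1 = 0.60 to p2 = 0.50 with ρ = 0.5. The share performing the behavior both times is

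p11 = p1·p2 + ρ√[p1(1 − p1)p2(1 − p2)] = 0.30 + 0.5 × √0.06 = 0.30 + 0.1225 = 0.4225.

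- Increasing: p2 − p11 = 0.50 − 0.4225 = 0.0775, or 7.8% (84 of 1080).
- Decreasing: p1 − p11 = 0.60 − 0.4225 = 0.1775, or 17.8% (192 of 1080).
- Net: 7.8% − 17.8% = −10 points.

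The Table 1 row would show the 7.8% only.

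**3. Why splitting by first report is not enough.** With no true change, the share increasing among those not performing the behavior at first is p(1 − p)(1 − ρ)/(1 − p) = p(1 − ρ). At p = 0.5 and ρ = 0.5 this is 25%. The matching share decreasing among those performing it is (1 − p)(1 − ρ), also 25%. These splits describe who could move, but only the net change is centered on zero under no change.

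**4. Increase asked directly.** If participants are simply asked whether they do more of something, steps 1 to 3 do not apply. The row is still one-sided, and the distortion becomes reporting bias. Staff administer the surveys unless the participant opts to self-complete, and the post-test survey follows immediately after the result. The Sample size section itself allows for social desirability bias in stated willingness to use such services.

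**The case against.** The strongest reply is that this is one descriptive row and that the rest of the plan looks in both directions. Much of that stands:

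- The Aim 1 modeling section begins "For participant survey binary outcomes, we will employ either population-averaged models" and goes on to logit models with a pre/post evaluation, whose coefficients can take either sign.
- The SCS substudy plans a "comparison of outcomes (i.e., overdose incidence and related risk behaviors) among frontline agency clients" who use SCS only, SCS and drug checking, or neither.
- The overdose outcome can rise.

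A reader might infer that the study as a whole cannot return no effect or harm. The documents do not support that. The cover is partial, however. If the Table 1 measure itself were the binary outcome in a model, no change and decrease would both be coded 0. The substudy draws on a cohort of people who inject drugs, is limited to those who consent to linkage, and lists no group using drug checking without SCS.

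A reader might also infer that all test results are pooled. The article does not say so: the post-test survey asks about responses to results, discarding toxic substances depends on the result, and tabulation by result is detail an article may leave to a fuller document.

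A third tempting step is to count anyone who increases on any of the six behaviors. With independent behaviors, the values in step 1 would then give a chance share of 12% to 69%. The article states no such composite rule and nothing to support independence, so those figures should not be used.

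Finally, the article does not define how an increase is reported, and discarding a tested drug is an event rather than a state that drifts between visits. This limits the fluctuation argument to behaviors compared across two reports.

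**Conclusion.** The point holds for this measure. A two-directional aim is served by a row that counts one direction; this is how the measure is fixed, not detail left out. Read as a difference between reports, it would show about 2% to 18% increasing per behavior with no true change, for prevalence 0.3 to 0.7 and correlation 0.3 to 0.9. It would show 7.8% increasing while caution fell by 10 points, at correlation 0.5. Those sizes rest wholly on assumed inputs. That the row cannot show a fall does not: it follows from the wording, however the increase is elicited. The consequence is limited to a non-primary measure and to claims of improved protective behavior based on it.

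**What to change.** For each behavior separately, replace the single proportion by the proportion increasing, the proportion decreasing and the net change, among participants with linked repeat reports. Show increases among those not performing the behavior at first intake and decreases among those performing it. Base any statement of improved protective behavior on the net change, and describe it as uncontrolled: without a comparator it remains open to time trends and reporting bias.

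Where numbers allow, also show the results by test result (unexpected or high-potency opioid detected, versus composition as expected), which answers the question the Discussion raises. Keep event-type responses, such as discarding the tested drug, as simple proportions by result.

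The change is mainly to analysis wording, provided each behavior is asked at repeat visits; the few intake items that the article names do not settle this. The costs are a less favorable headline figure, thin strata, and restriction of paired change to clients who return and use their identifier. The Limitations section says linkage depends on clients' willingness to create and use one, and the Sample size section says the split between unique and repeat clients is unknown. The number contributing to each paired figure should therefore be reported beside it.

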### Study partners

Three frontline harm reduction agency partners—Parkdale Queen West Community Health Centre (Queen West site), South Riverdale Community Health Centre, and The Works at Toronto Public Health—have been funded as DCS intake sites. With the exception of The Works, which is a public health agency, the remaining two partnering frontline agencies are community health centers, and all agencies combine harm reduction service delivery with access to other services, including primary care, mental health care, and social service programs. As DCS intake sites, agencies will collect drug samples from participants, administer intake and post-test surveys, facilitate transport of samples to clinical laboratories, and communicate analysis results to participants along with relevant harm reduction information. Notably, Parkdale Queen West Community Health Centre (Queen West site) also houses TRIP Project, a program providing information and resources on harm reduction and safer sex to youth in nightlife and party settings.

Clinical laboratory partners at the Centre for Addiction and Mental Health and St. Michael's Hospital—two urban hospitals with specialized programs for substance use—will analyze samples of drugs from participants at frontline harm reduction agencies using LC- and GC-MS techniques and guide the aggregation of analysis data across sites to identify composition (qualitative and quantitative) trends in the unregulated drug supply.

To bolster the relevance of findings and ensure effective knowledge translation strategies that address the needs of key populations, a Community Advisory Board made up of people who use drugs will advise on all aspects of the design, analysis, interpretation, and knowledge translation activities of this study [39]. Additionally, protocols for research methods and outcome measures will be aligned as much as possible with DCS implemented in other Canadian jurisdictions, including British Columbia and the capital city of Ottawa, Ontario, to maximize the potential comparability of findings across distinct settings.

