#### Sample size (Aim 1)

In lieu of randomization, which is neither feasible nor ethical given the type of service to be examined in the present study, a community recruitment model will be employed whereby a survey of all consenting DCS clients is undertaken (i.e., the sampling frame consists of all clients of DCS). Since study participants are recruited “passively” through their use of the service, we are unable to estimate the proportion of surveys to be obtained from unique versus repeat clients until after DCS are implemented. We therefore cannot determine the total person-time data that will be collected. We note, however, that 75% of feasibility survey respondents recruited from frontline agencies reported being willing to access DCS. The total population of structurally vulnerable people who use drugs in Toronto is estimated at 9000, among whom 20% are willing to use SCS [35]; it is estimated that *n* = 1800 unique individuals who use drugs access frontline agencies. Previous literature suggests social desirability bias in reports of willingness to access harm reduction services [40]; we therefore estimate an approximate total of *n* = 1080 DCS clients.

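### The one listed composition measure for Aim 3, a trend aim, is a raw count with no denominator, so it moves with the volume of samples in either direction

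*Protocol article*

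**What the plan says.** Table 1 (Methods, Approach) heads the third block of measures "Aim 3: Identify trends in the composition (qualitative and quantitative) of the unregulated drug supply in Toronto". Its first row is the "Number of analysis results detecting composition different from participant expectations", drawn from the intake survey and the laboratory data. The other two rows in the block concern the accuracy and timeliness of alerts, and the spatial association between DCS sites and fatal overdose. The first row is thus the only listed measure of what the samples contain.

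Two Aim 1 rows in the same table are written on a different scale: "Proportion of participants reporting increase in protective behaviors" and "Proportion of participants reporting they gained, intend to use, and/or used knowledge and skills".

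Elsewhere, Study partners says that the laboratories will "guide the aggregation of analysis data across sites to identify composition (qualitative and quantitative) trends in the unregulated drug supply", with no rate or share mentioned. The section on analysis of drug samples covers laboratory technique and turnaround. The two Aim 3 parts of the Analytic plan use only coroner and paramedic data.

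On volume, the Abstract describes "a network of DCS launched in 2019 to prevent overdose and overdose-related risk behaviors". Sample size (Aim 1) states that "we are unable to estimate the proportion of surveys to be obtained from unique versus repeat clients until after DCS are implemented", and Limitations adds that "it is not possible to estimate the number of individuals that will access DCS and provide data".

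**The concern.** A trend in supply composition has to be read against the number of samples examined. A bare count mixes two things: how often a sample is not what the client expected, and how many samples were brought in. Only the first says anything about the drugs. The second depends on how many clients come, how often they return, and how many consent to the intake survey, because the expected substance is recorded there and clients who decline consent still receive the service (Ethics, consent, and permissions).

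Read as a supply trend, the count could suggest deterioration when only uptake has grown, or stability when the supply has worsened and uptake has dropped. Counts from services of different size are also hard to set side by side, although Study partners wants outcome measures aligned with those of other Canadian jurisdictions.

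**Working it through.** The article gives no expected count, rate or sample size for this measure, so there is no figure of its own to reproduce. The check is algebra plus an illustration with assumed inputs.

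**Formula.** For period *t*, expected count C_t = p_t × n_t, where p_t is the discordant share and n_t the number of analysed samples with a recorded expectation. Between two periods, C_2/C_1 = (p_2/p_1) × (n_2/n_1). If the share is constant, the ratio of counts is simply the ratio of volumes.

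**Inputs.** From the article: the scale of the measure (a number), the trend aim, a service launched in 2019, and client numbers and repeat use that cannot be estimated in advance. Assumed, because the article gives no values: p of 10%, 30% or 50%; 200 samples in the first period; volume multiplied by 1, 1.5, 2 or 3.

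**Constant share, changing volume.**

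| Share | n = 200 | n = 300 | n = 400 | n = 600 |
|---|---|---|---|---|
| 10% | 20 | 30 | 40 | 60 |
| 30% | 60 | 90 | 120 | 180 |
| 50% | 100 | 150 | 200 | 300 |

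Every row grows by the volume factor alone. The proportion does not move: 60/200 = 120/400 = 180/600 = 30%.

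**Share and volume moving in opposite directions.**
- Share falls, volume doubles: 0.40 × 200 = 80, then 0.25 × 400 = 100. The ratio is 0.625 × 2 = 1.25, so the count rises by a quarter while discordance falls.
- Share rises, volume halves: 0.30 × 400 = 120, then 0.45 × 200 = 90. The ratio is 1.5 × 0.5 = 0.75, so the count falls by a quarter while discordance rises.

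**How often a naive comparison would mislead.** The article specifies no test. If someone compared two counts as Poisson at the two-sided 5% level, the standardised difference would be d = (C_2 − C_1)/√(C_1 + C_2), and the chance of declaring a difference Φ(d − 1.96) + Φ(−d − 1.96). At p = 30%, 60 against 90 gives d = 30/√150 = 2.45 and 69%; 60 against 120 gives d = 60/√180 = 4.47 and 99%. With doubled volume at p = 10%, 20 against 40 gives d = 20/√60 = 2.58 and 73%. At unchanged volume the figure is the nominal 5%.

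**What a proportion does not cure.** The overall share is a weighted mean of the shares for each expected drug, the weights being the mix of drugs submitted. If that mix shifts, the overall proportion can move with no change within any drug.

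**The case against.** The row is a one-line label in a condensed article. No trend analysis of the count is written anywhere, the Poisson comparison above is an illustration rather than the plan's method, and the full protocol may well report a share. Table 1 is also loose about scale: self-reported overdose carries none in the table, yet the Analytic plan models it as binary. The word for a number may therefore be less deliberate than it looks. A count of unexpected results is a fair output measure for a service meant to reveal unexpected substances, and Study partners shows that composition data will be aggregated beyond this one row.

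Much of this stands, and it limits the point. A reader might infer that the study will report a worsening supply because uptake grows. The documents do not support that: they never say that uptake will rise, they state no test on the count, and the error can run either way. The statement on unique and repeat clients concerns Aim 1 surveys and bears on sample volume only indirectly. A reader might also infer that Aim 3 cannot be met or that comparison with other jurisdictions is ruled out. Neither follows, since the data for a proportion are collected anyway.

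What does not stand is the argument that this is only detail left to the full protocol. The article names a scale for this row, that scale cannot by itself carry a trend, and no other section supplies a denominator.

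**Conclusion.** The point holds in a limited form. The only composition measure listed for a trend aim is a count that confounds volume with supply. With a constant share, the distortion equals the ratio of sample volumes: a doubling of samples doubles the count. When share and volume move in opposite directions, the count can point the wrong way (80 to 100 with a falling share, 120 to 90 with a rising one). These sizes rest on assumed shares and volumes; the algebra does not. The fault lies in the definition, not in any stated test, and its direction in practice is unknown. The measure is not primary, and no sample size or stated test depends on it, so this is a minor correction.

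**What to change.** Reword the Table 1 row along these lines: *Number and proportion of analysed samples with a recorded participant expectation whose composition differs from that expectation, by calendar period.* Report the denominator for each period beside the count. Show results by expected drug as well, because the proportion removes the effect of volume but not of a changing case mix. Word conclusions as trends in samples submitted to DCS, not in the supply as a whole. Standardisation by site and intervals allowing for several samples per client can be left to the analysis plan; they are not part of this correction.

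The cost is one table row and a simple tabulation. The intake survey already asks at every visit what the client believes the substance to be, and the samples are analysed in any case, so no new data are needed.
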